Randomisation is performed by a central website based computer program in 1:1 ratio (Fig. 1) and stratified by type of hospital (university medical centre versus non-university medical centre), age (below 65 years or 65 years and older), and symptom duration (shorter than 0.5 year or 0.5 year and longer), using variable permuted blocks. Study personnel, research nurses, neurologists, and patients are blinded to the treatment allocation at all times. ACE Apothecary (ACE Apotheek, Zeewolde, The Netherlands) allocates the randomised patient to a medication number that corresponds with the treatment group and ACE Apothecary is responsible for packaging, labelling and shipment of the study medication during the first 42 weeks of the study. Randomisation data are kept strictly confidential and are accessible only to authorised persons at ACE Pharmaceuticals and ACE Apothecary until the database is unlocked at the end of the study. All data will be entered in a central website based database before the database is unlocked.

Approval of the medical ethical committee of the Academic Medical Center was obtained. The LEAP-study is conducted according to the principles of the Declaration of Helsinki (version 2008). Study monitoring and data management are performed in accordance with the International Conference on Harmonisation - Good Clinical Practice guidelines. This is an investigator-initiated study. None of the funding organisations has influence on the design or execution of the trial, the analysis of the study data, or the publication of articles concerning the study data.

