### Outcome measures

The primary clinical outcome measure is the difference in the mean total Unified Parkinson’s Disease Rating Scale (UPDRS) scores between the early- and delayed-start groups at 80 weeks (Table 2) [8]. Secondary endpoints are (a) progression of symptoms between Visit 2 and Visit 4 (phase 1) and between Visit 5 and Visit 8 (phase 2) measured with the UPDRS; (b) disability measured with the AMC Linear Disability Score (ALDS), defined as the between-group difference at 80 weeks (Table 2) [9]; (c) between-group difference in mean total UPDRS scores at 80 weeks and the progression of UPDRS scores during phases 1 and 2 in patients who followed the study ‘per protocol’; (d) between-group difference in mean total UPDRS scores at 80 weeks and the progression of UPDRS scores during phases 1 and 2 in patients with UPDRS scores in the highest quartile of scores at baseline who followed the study ‘per protocol’; (e) number of patients that need additional medication during phases 1 and 2; (f) cognitive impairment, measured with the MMSE (Table 2) [10]; (g) depression, measured with the BDI-II (Table 2) [11]; (h) perceived quality of life measured with the Parkinson’s Disease Questionnaire-39 (PDQ-39) (Table 2) [12]; (i) quality adjusted life years (QALY), after applying existing scoring algorithms to derive health utilities from observed European Quality of Life-5 Dimensions (EQ-5D) data (Table 2) [13]; (j) working status and absence from paid work measured with a standardised questionnaire; (k) caregiver burden with a standardised questionnaire; (l) resource utilisation outside of the participating hospitals measured with a standardised questionnaire (for (j), (k) and (l) we used an adjusted version of the Short Form - Health and Labour Questionnaire [14, 15] and iMTA Valuation of Informal Care Questionnaire targeted at the study population [16]); (m) costs per unit decrease of the UPDRS and costs per QALY [17, 18]; (n) number of patients withdrawn from the study or lost to follow up; (o) dyskinesias, measured with items 32 to 35 of the UPDRS part IV; (p) levodopa-induced motor response fluctuations throughout the course of the study measured with items 36 to 39 of the UPDRS part IV and three standardised questions concerning wearing-off phenomena (q) (serious) adverse events defined as the frequency, severity, nature, and duration of any adverse event throughout the course of the study.

**Table 2 Tab2:** Clinical rating scales

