### Statistics

Based on the ELLDOPA study, we assume a mean baseline UPDRS score of 28 points with a standard deviation of 13 points and anticipate a mean UPDRS score in the early-start group of 31 points (worsening of 3 points during follow-up) and a mean UPDRS score in the delayed-start group of 35 points (worsening of 7 points) at the final outcome assessment at 80 weeks [3]. Assuming that the common standard deviation is 13, a sample size of 167 in each group will have 80 % power to detect a difference in mean follow-up scores of 4 points, using a two-group *t*-test with a 0.05 two-sided significance level. In the ELLDOPA study, a dropout rate of 22.2 % was reported in the placebo group [3]. After 80 weeks, the ADAGIO-study reported a total dropout rate of 24.4 % in the 1 mg delayed-start group and 19.2 % in the 2 mg delayed-start group. Based on these results, a total withdrawal rate of 25 % was considered realistic [19]: therefore, we plan to include 223 patients per treatment arm, which means 446 patients in total (Fig. 3).

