**Fig. 3 Fig3:**
[figure not shown]
Flow chart LEAP-study. Taking into account a withdrawal rate of 25 %, 446 patients need be enrolled to be able to show a minimal clinically relevant difference of four points on the total UPDRS at the end of the study

Data will be analyzed according to the intention-to-treat principle. The main analysis of this trial consists of a comparison between the trial treatment groups of the primary outcome after 80 weeks. First, the follow-up difference of mean UPDRS scores between the treatment arms will be crudely analyzed using a two-group *t*-test. Second, the UPDRS follow-up scores will be further investigated using analysis of covariance (ANCOVA), taking into account patients’ UPDRS baseline values. To account for the repeated measures within patients, a random effects model will be used.

With regard to the comparisons of the secondary outcome progression of symptoms during phases 1 and 2 we planned two separate analyses using a random effects model to account for the repeated measures within patients (Fig. 2). For phase 1, we will use the measurements of Visit 2 (4 weeks), Visit 3 (22 weeks) and Visit 4 (40 weeks) to estimate the difference in slopes between the two treatment groups. A more progressive course (steeper upward slope) in the placebo group during phase 1 can reflect disease-modifying effects of levodopa. This will be further explored by examining the slopes of phase 2. Equal steepness of the slope during phase 2 indicates that the (assumed) effect found in phase 1 is a true disease-modifying effect. Therefore, we will use measurements of Visit 5 (44 weeks), Visit 6 (56 weeks), Visit 7 (68 weeks), and Visit 8 (80 weeks) to test equality of progression in phase 2 with a non-inferiority test on the difference between the slopes of the two treatment arms using a non-inferiority margin of 0.055 UPDRS points difference in increase per week (Fig. 2). The slopes of the phases 1 and 2 will be analysed by both an intention-to-treat and a per-protocol approach (see below for further explanation).

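### The week-80 primary comparison leads with an unadjusted t-test, places baseline adjustment second, uses no randomisation stratum in any stated model, and names no confirmatory result

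*Protocol article*

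**What the plan says.** Under Outcome measures, the primary outcome is the contrast of the two arms on average total UPDRS at week 80.

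Under Statistics, the sample size is built on the unadjusted comparison. The article states that "a sample size of 167 in each group will have 80 % power to detect a difference in mean follow-up scores of 4 points". The calculation takes an SD of 13 in both arms and an unadjusted t-test at the two-sided 5% level.

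The analysis paragraph that follows the Fig. 3 legend gives the order. In first place, the difference in follow-up means "will be crudely analyzed using a two-group" test, namely the t-test. In second place, the scores at follow-up "will be further investigated using analysis of covariance (ANCOVA"), with baseline UPDRS as the covariate. The next sentence adds a random-effects model for the repeated measurements and does not say how it relates to the other two.

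Under Study procedures and randomisation, allocation is 1:1. It is "stratified by type of hospital (university medical centre versus non-university medical centre), age (below 65 years or 65 years and older), and symptom duration". The Statistics section uses hospital type, age and disease duration for subgroup analyses. They appear in no stated model of the week-80 comparison.

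**The concern.** The analysis listed first uses the least information. Baseline UPDRS is measured on the same scale as the outcome and should predict it. The Discussion itself gives prognostic reasons for two strata: progression differs by age, and patients with longer disease duration are expected to need added medication sooner. Leaving such variables out of the lead analysis makes its standard error larger than it need be and leaves chance baseline differences in the lead estimate.

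The text also orders the analyses without saying which one decides the trial. If the t-test and the ANCOVA fell on opposite sides of 0.05, the article would support an argument for either. A single sentence naming the confirmatory result would prevent that dispute.

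**Working it through.** **Inputs.** From Statistics: difference 4 points, common SD 13, 167 evaluable per arm, two-sided 0.05, 80% power, 25% withdrawal. From Study procedures and randomisation: 1:1 allocation. The correlation r between baseline and week-80 UPDRS is not given, so it is **assumed** to lie between 0.3 and 0.7.

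**Step 1: reproduce the plan's figure.**
- SE of the difference = 13 × √(2/167) = 1.423 points.
- Noncentrality = 4 / 1.423 = 2.81 on 332 degrees of freedom. Power by the noncentral t distribution is 80.05%. At 166 per arm it is 79.8%, so 167 is the smallest sufficient number.
- Enrolment = 167 / 0.75 = 222.7, rounded up to 223 per arm, 446 in total.

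The stated figures are correct for the unadjusted t-test.

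**Step 2: adjust for baseline.** Residual SD = 13 × √(1 − r²). SE = residual SD × √(2/167). The 95% half-width is 1.967 × SE (t quantile, 332 degrees of freedom). The one degree of freedom spent on the covariate is negligible.

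| r (assumed) | Residual SD | SE | Power for 4 points | 95% CI half-width |
|---|---|---|---|---|
| 0 (t-test) | 13.00 | 1.423 | 80.1% | 2.80 |
| 0.3 | 12.40 | 1.357 | 83.6% | 2.67 |
| 0.5 | 11.26 | 1.232 | 89.9% | 2.42 |
| 0.7 | 9.28 | 1.016 | 97.5% | 2.00 |

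These figures are for a week-80 ANCOVA on baseline alone. Any further gain from the strata or from the repeated measurements is not counted.

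**Step 3: effect of omitting the strata.** If the strata explain a share s of the outcome variance (assumed), stratified randomisation makes the true variance of the difference about (1 − s) times what the t-test uses. The actual type I error is then 2 × [1 − Φ(1.96 / √(1 − s))]. For s = 2%, 5% and 10% this gives 4.8%, 4.4% and 3.9%. The test is conservative, never inflated.

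**Step 4: what hangs on naming the confirmatory result.** The t-test and ANCOVA statistics correlate √(1 − r²). I simulated pairs of normal statistics with that correlation.
- With no true effect, if *either* result could be claimed at 0.05, the type I error would be about 6.4% at r = 0.3, 7.3% at 0.5 and 8.2% at 0.7.
- With a true 4-point effect, the two disagree on significance in about 7%, 12% and 18% of trials respectively. In most of these the ANCOVA is significant and the t-test is not.

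**The case against.** The strongest reply is that nothing here is an error. The t-test is unbiased under randomisation, the trial was sized for it, and it delivers the 80% power promised. This stands in full: the point concerns efficiency and clarity, not validity.

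A reader might infer that the plan ignores baseline and throws its precision away. It does not. The ANCOVA on baseline is prespecified in the very next sentence, so the adjusted estimate is placed second, not lost.

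A reader might also infer three unranked primary analyses. The text does not support that either. It gives an order, its wording suggests that the ANCOVA follows up the t-test, and the sample size names the t-test. The random-effects sentence follows directly on the ANCOVA and may only describe how the adjusted model is fitted, so there may be two analyses. On the natural reading the t-test is confirmatory, and the error rates in the last step of the working would not arise. What remains is that the article never says so outright.

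Two further replies have weight. The size of the gain depends on a correlation that the article does not give. Extra levodopa during the placebo phase and later discretionary medication, both allowed under Study procedures and randomisation, could weaken it, which is why the range starts at 0.3. Also, a covariate list is commonly left to the full protocol or the analysis plan, which are not shown, so the absence of the strata would be a weak point alone. It counts here because the article does state its analyses and their order, and puts the least efficient one first.

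**Conclusion.** The point holds as an improvement worth making, not as a fault that endangers the trial. The lead week-80 analysis is unadjusted, baseline adjustment is secondary, the strata enter no stated week-80 model, and the confirmatory result is not expressly named.

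The cost is efficiency. Against 80% power for the t-test, adjustment for baseline would give about 84% at r = 0.3, 90% at 0.5 and 97.5% at 0.7, with intervals narrower by 0.13, 0.38 and 0.80 points on each side (2.80 minus 2.67, 2.42 and 2.00). This rests on the assumed correlation, on an SD of 13 at week 80, and on 167 evaluable patients per arm. Even the low end of the range is a gain without cost.

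The documents do not support a claim that the trial is underpowered, that the t-test is biased, or that its type I error is inflated.

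**What to change.** Before unblinding, state one confirmatory analysis: the treatment contrast at week 80 from the random-effects repeated-measures model already planned, with baseline UPDRS and the three stratification factors as covariates. Visit should be a categorical factor with a treatment-by-visit term, so that the contrast still estimates the stated week-80 difference.

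Code the strata as randomised: hospital type, age at the 65-year cut, and symptom duration at the 0.5-year cut. The last needs saying because the randomisation text refers to symptom duration, while the subgroup and Discussion text refers to disease duration.

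Make the week-80 ANCOVA with the same covariates a sensitivity analysis, and label the crude t-test as supportive only.

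The cost is a few sentences. Baseline UPDRS is already collected, the strata are known at randomisation, and no patients or visits are added. The sample size can stay at 223 per arm, where the t-test calculation becomes a conservative basis.

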As pointed out earlier, the main outcome in this study will be the comparison between treatment arms on UPDRS scores after the total study period of 80 weeks, since this outcome relates to clinical practice. A difference of four points on the total UPDRS is considered to be clinically relevant [20]. The comparisons of slopes in the secondary analyses serve only to differentiate between the different types of treatment effects (direct symptomatic vs disease modifying). Here we pre-specify the possible inference made on these secondary analyses:if a faster progression is found in the placebo group during phase 1 and the non-inferiority assumption assuming equal progression is met in phase 2, this will be indicative of a true disease-modifying effect;if a faster progression is found in the placebo group during phase 1, but non-inferiority of slopes during phase 2 is not demonstrated, then the results are indicative of only direct symptomatic effects.

With regard to the comparisons of the other secondary outcomes (disability, number of patients that need additional medication for PD, cognitive impairment, mood, quality of life, ability to (maintain) work, use of (informal) care, caregiver burden, levodopa-induced response fluctuations, and side effects), we will use the appropriate parametric and nonparametric statistics. Cost-effectiveness and cost-utility analyses will be performed from a societal perspective with the costs per unit decrease on the UPDRS respectively, the costs per QALY as outcomes. In all analyses statistical uncertainties will be expressed in 95 % confidence intervals.

Subgroup analyses by type of hospital (university medical centre versus non-university medical centre), age and disease duration will be performed. Finally, two additional ‘per protocol’ analyses will be carried, focusing on (a) between-group difference in UPDRS scores at 80 week and the progression of UPDRS scores during phases 1 and 2, and (b) between-group difference in UPDRS scores at 80 weeks and the progression of UPDRS scores during phases 1 and 2 in patients in the highest quartile of scores at baseline. Patients will be excluded from the per protocol analysis if they needed additional PD-medication during the study, if they did not use the correct dose and type of medication (e.g., extended release levodopa formulations), or if they missed either Visits 1, 2, 4, 5 or 8.

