Third, the placebo-controlled phase of 40 weeks was chosen based on the results of the ELLDOPA study, which suggested a possible disease modifying beneficial effect of levodopa evident after 40 weeks of treatment [3]. Ideally, the placebo-controlled phase of 40 weeks would even be longer because if a disease modifying effect of levodopa exists, there would then be more time for the slopes of the two treatment groups to diverge further (Fig. 2). However, because of symptom progression, a placebo-controlled phase of more than 40 weeks would result in the retention of progressively fewer patients in the placebo-controlled phase of the study, making the placebo-controlled phase only slightly longer because of the increasing lower numbers in the delayed-start group – thereby diminishing the theoretical advantage of a longer placebo-controlled phase. More importantly, poorer retention in the delayed-start group would compromise the ability to show a difference between the two groups and would potentially select out patients with a milder or more slowly progressive disease course, thereby diminishing a possible existing difference between the two groups. Also, a longer placebo-controlled phase would result in higher costs in this investigator-initiated study. A study design with an additional delayed-stop (at 40 weeks) arm was rejected because this would require patients that typically need antiparkinson medication at this point would experience increased disability and discomfort due to having treatment withheld.

Fourth, we chose a daily levodopa/carbidopa dose of 300/75 mg. In the ELLDOPA study, three levodopa/carbidopa doses (150/37.5 mg, 300/75 mg or 600/150 mg daily) were tested and compared with placebo for 40 weeks, followed by a two-week washout period. The results suggested a beneficial disease modifying effect of levodopa in all treatment groups, thereby making a strong case to choose the 150/37.5 mg daily dose for the current study. However, in the 150/37.5 mg group, there was also a higher dropout rate [3]. We considered a daily treatment of levodopa/carbidopa 600/150 mg too high because of the risk of more side effects [24] and because in daily practice, starting-doses of levodopa are usually lower.

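### The phase 2 slope model uses Visits 5–8 alone, so score-dependent withdrawal before week 44 can bias the phase 2 non-inferiority test

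*Protocol article*

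**What the plan says.** Protocol article, Methods, Statistics: for progression during the two phases, "we planned two separate analyses using a random effects model to account for the repeated measures within patients". For phase 1, "we will use the measurements of Visit 2 (4 weeks), Visit 3 (22 weeks) and Visit 4 (40 weeks"; for phase 2, "we will use measurements of Visit 5 (44 weeks), Visit 6 (56 weeks), Visit 7 (68 weeks), and Visit 8 (80 weeks". Phase 2 is tested for non-inferiority "using a non-inferiority margin of 0.055 UPDRS points difference in increase per week". The population is described thus: "The slopes of the phases 1 and 2 will be analysed by both an intention-to-treat and a per-protocol approach".

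The same section fixes how the result is read. If progression is faster on placebo in phase 1 and phase 2 non-inferiority is met, this indicates disease modification. If instead "non-inferiority of slopes during phase 2 is not demonstrated, then the results are indicative of only direct symptomatic effects".

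The sample size paragraph allows for 25% withdrawal in total, with no split by arm or by phase. Study procedures and randomisation aims to continue all measurements in patients who depart from the protocol.

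**The concern.** A likelihood-based random effects model treats withdrawal as ignorable only given the data inside that model. The phase 2 model, as described, starts at week 44. Suppose that patients who worsened during phase 1 are more likely to leave before week 44, and that a patient's phase 1 and phase 2 slopes are correlated. The patients left in phase 2 are then a selected group, and the model holds nothing that could correct for it. Where selection differs between arms, the slope contrast shifts even if the true phase 2 slopes are equal.

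The stake is the label on the trial's mechanistic result. The phase 2 test decides between disease modification and a symptomatic effect only, which is the distinction that the delayed-start design exists to draw. Scores already collected at Visits 1–4 could reduce the risk but are not used.

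**Working it through.** **1. The plan's own figure.** Difference 4, SD 13, two-sided 0.05: the exact t-test power is 0.798 with 166 per arm and 0.801 with 167, so 167 is right. 167 / 0.75 = 222.7, so 223 per arm and 446 in total. The sample size reproduces and is untouched by this point.

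**2. Loss before week 44.** At constant hazard (an assumption), 25% by week 80 gives 1 − 0.75^(44/80) = 0.146 by week 44, and 0.146 × 446 ≈ 65 patients.

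**3. Direction.** Let a share x of an arm, those with the worst phase 1 scores, leave before week 44. Let s be the between-patient slope SD and r the correlation of the phase 2 slope with that score. The mean slope among those who stay falls by r·s·φ(z)/(1 − x), where z is the normal quantile for x. The factor φ(z)/(1 − x) is 0.109 at x = 5%, 0.195 at 10% and 0.274 at 15%. The bias, early minus delayed, is r·s × (delayed factor − early factor):

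| Lost early / delayed | r = 0.3, s = 0.10 | r = 0.6, s = 0.15 |
|---|---|---|
| 10% / 10% | 0 | 0 |
| 5% / 10% | +0.0026 | +0.0078 |
| 5% / 15% | +0.0050 | +0.0149 |
| 15% / 5% | −0.0050 | −0.0149 |

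The sign depends on which arm loses its faster progressors. The values of r, s and the arm split are assumptions.

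**4. Size by simulation.** From the document: 223 per arm, the visit weeks, the 0.055 margin and 95% intervals (non-inferiority is taken as an upper 95% limit below 0.055). Assumed: residual SD 5, slope SD as shown, correlation of phase 1 and phase 2 slopes 0.5 or 1, and withdrawal logistic in the observed change from baseline. The true phase 2 slope difference is 0. Withdrawal is total by week 80 except where marked.

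| Setting | Bias of Visits 5–8 model (points/week) | Share of margin |
|---|---|---|
| Withdrawal near the cited rates, slope SD 0.10–0.15 | about 0 to 0.004 in one set of runs, 0 to 0.008 in another | up to 0.008/0.055 = 15% |
| Delayed about 30–33%, early 16–20%, slope SD 0.10–0.15 | about 0 to 0.012 | up to 22% |
| Before week 44: delayed 13–23%, early 5–11%, slope SD 0.05–0.15 | about 0 to 0.0145 | up to 26% |
| Delayed 29–34%, early 17–20%, slope SD 0.10–0.20 | about 0 to 0.017 | up to 31% |
| Loss equal and unrelated to score, slope SD 0.10 | 0.0007 (Monte Carlo noise) | about 0 |

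An analysis that also used the earlier scores stayed within 0.003 of zero throughout. The article gives no early-arm rate: its cited 24.4% and 19.2% both come from delayed-start groups. The first row therefore assumes 25% in each arm, or 24.4% delayed against 19.2–22% early, and similar splits.

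**5. Effect on the test.** Approximate probability of showing non-inferiority = Φ((0.055 − bias)/SE − 1.96). The simulated SE was about 0.0217 at slope SD 0.10 and 0.0245 at 0.15.

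| Bias | SE 0.0217 | SE 0.0245 |
|---|---|---|
| 0 | 0.72 | 0.61 |
| 0.004 | 0.65 | 0.55 |
| 0.008 | 0.58 | 0.48 |
| 0.012 | 0.51 | 0.42 |

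A bias of 0.008 thus costs about 13 to 14 percentage points. In direct simulation, the separate model showed non-inferiority 0–6 points less often than the joint model in the runs with bias up to 0.004. With larger arm imbalance and slope SD 0.10–0.15, the gap reached about 20–25 points.

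**6. Rescue.** Letting worsening delayed-arm patients be rescued and stay in follow-up (an assumed mechanism; slope SD 0.15, correlation 1) cut the bias from 0.0064 to 0.0031. The separate and joint non-inferiority rates moved from 45% and 56% to 51% and 57%.

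**The case against.** The strongest reply is that nothing in the article shows the bias will occur. It needs severity-driven loss before week 44, more of it from one arm, and correlated phase slopes with real spread. The document gives none of these. That stands, and it limits the point to what can happen.

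A reader might infer from the Discussion that the authors expect such loss, since it says "poorer retention in the delayed-start group would compromise the ability to show a difference between the two groups". The text does not support that. It explains why a placebo phase longer than 40 weeks was rejected, and it concerns staying in the placebo-controlled phase rather than leaving the trial. It shows that the mechanism is plausible, not that it is forecast for the chosen design.

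Patients who need more treatment are meant to stay in follow-up, so worsening need not end in withdrawal. This reduces the bias (step 6) but does not remove the 25% withdrawal that the plan allows for.

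The full protocol may name covariates or missing-data methods that the article omits. That is possible. Still, the separate models and their visits are stated choices, not silence. Nor does analysing the available patients as randomised contradict the intention-to-treat label, and no such contradiction is claimed.

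Finally, even without bias the test fails in roughly 28–39% of trials with equal slopes (step 5, first row). That imprecision is a separate matter and should not be charged to this choice.

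**Conclusion.** The point holds as a conditional one. Fitting phase 2 on Visits 5–8 alone means that withdrawal before week 44 which depends on baseline or phase 1 scores is not ignorable in that model. The bias can go either way, and it is about zero if loss is equal or unrelated to score.

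With assumed slope SDs of 0.10–0.15 points per week, it is about 0 to 0.008 points per week at withdrawal rates like those cited. It reaches about 0.012–0.017 with larger arm imbalance; the top value comes from runs that also allowed a slope SD of 0.20. Continued follow-up of rescued patients lowers these figures.

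A reader might infer that the plan is certain to favour a symptomatic-only conclusion. The documents do not support this: they give no withdrawal by arm or phase and no slope variation, and selective loss of faster progressors from the early-start arm would favour a disease-modification claim instead. The slopes are secondary, and the primary week-80 comparison is not affected.

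**What to change.** Take the intention-to-treat slope contrasts for both phases from one likelihood-based repeated-measures model over all eight visits, with:

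- a common baseline mean at Visit 1;
- arm-by-visit means at weeks 4, 22 and 40, with the phase 1 slope as a contrast of them. For these equally spaced visits the least-squares slope is (week 40 mean − week 4 mean)/36. Free visit means avoid forcing a straight line through phase 1 when some patients are rescued;
- an arm-specific intercept and linear slope over weeks 44–80;
- an unstructured covariance, or correlated patient-level slopes for the two phases.

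Keep the 0.055 margin, and report the two separate models as a sensitivity analysis.

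The cost is wording and a somewhat larger model, with no new patients, visits or data. Without withdrawal the slopes are practically unchanged. The downsides are that a covariance across phases must be specified and estimated, and that the model corrects only for loss explained by observed scores. It does not cure the per-protocol slope analysis, which excludes patients who needed additional medication or missed key visits.

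### A pass of the phase 2 slope test excludes a relative loss of 1.98 points or more; it does not show equal progression, and by itself it cannot establish a maintained effect when the phase 1 gain is about 2 points or less

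*Protocol article*

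**What the plan says.** All references are to the protocol article, Methods, Statistics.

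- **Phase 1 slopes** use weeks 4, 22 and 40: "we will use the measurements of Visit 2 (4 weeks), Visit 3 (22 weeks) and Visit 4 (40 weeks".
- **Phase 2 slopes** use weeks 44, 56, 68 and 80: "we will use measurements of Visit 5 (44 weeks), Visit 6 (56 weeks), Visit 7 (68 weeks), and Visit 8 (80 weeks". The article describes this comparison as a test of equal progression, carried out by non-inferiority and "using a non-inferiority margin of 0.055 UPDRS points difference in increase per week".
- **Inference rule.** The list of pre-specified inferences covers the case where placebo worsens faster in phase 1. If in addition "the non-inferiority assumption assuming equal progression is met in phase 2, this will be indicative of a true disease-modifying effect".
- **Yardstick.** The trial is sized "to detect a difference in mean follow-up scores of 4 points", and the same figure is the threshold of relevance: "A difference of four points on the total UPDRS is considered to be clinically relevant".

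The rule sets no minimum phase 1 gain, does not relate the margin to the gain observed, and does not depend on the week 80 result. The same section says that week 80 is the main outcome and that the slopes serve only to separate symptomatic from disease-modifying effects.

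**The concern.** A non-inferiority test answers a bounded question: is early start worsening faster than delayed start by the margin or more? The article attaches a different answer to a pass, namely that the two arms progress equally and hence that the phase 1 effect is truly disease modifying.

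The gap matters because the margin is a fixed number, while the amount that could be lost is whatever phase 1 produced. With a gain near 4 points, excluding a 2-point loss says something useful. With a gain of 2 points or less, the same pass is compatible with the gain disappearing by week 80. The slopes are secondary, but the article gives them the task of telling the two types of effect apart, which is the reason for the delayed-start design.

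**Working it through.** **Inputs from the article.** Margin 0.055 points/week; phase 2 window 80 - 44 = 36 weeks; phase 1 window 40 - 4 = 36 weeks; target difference 4 points; SD 13; 167 per group; 25% withdrawal.

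**The plan's own sample size reproduces.** The normal approximation gives n = 2 x (1.96 + 0.8416)² x 13² / 4² = 165.8, so 166 per group. The exact t-test solution is 166.8, so 167. Then 167 / 0.75 = 222.7, so 223 per arm and 446 in total.

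**The margin in points**, taking slopes as linear over the window:
- 0.055 x 36 = 1.98 points.
- 1.98 / 4 = 49.5% of the target.
- Half of a 4-point gain over 36 weeks is 4 / 36 / 2 = 0.0556/week, almost exactly the margin.

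**What a pass secures for a given true phase 1 gain** (gain - 1.98):

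| Phase 1 gain over 36 weeks | Least that remains after a loss at the margin |
|---|---|
| 4 points | 2.02 |
| 3 points | 1.02 |
| 2 points | 0.02 |
| 1.5 points | -0.48 |

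Break-even is a gain of 1.98 points.

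**How often both legs of the rule pass.** The article gives no standard error (SE) for a slope difference, so 0.015, 0.020 and 0.025 points/week are assumptions. I also assume equal SEs and independent estimates in the two phases, a two-sided 5% test in phase 1, and an upper 95% limit below 0.055 in phase 2. With true gain g and true loss l per week:

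P = Φ(g/SE - 1.96) x Φ((0.055 - l)/SE - 1.96)

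Example with g = 0.06, l = 0.03, SE = 0.015: Φ(2.04) x Φ(-0.29) = 0.979 x 0.385 = 0.38.

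| True situation | SE 0.015 | SE 0.020 | SE 0.025 |
|---|---|---|---|
| Gain 0.055, all being lost (l = 0.055) | 2.4% | 2.0% | 1.5% |
| Gain 0.06 (2.2 points), half being lost | 38% | 20% | 11% |
| Gain 0.06, two thirds being lost | 17% | 10% | 6% |
| Gain 0.10 (4 points over 40 weeks), half being lost | 5% | 4% | 4% |

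**What must be observed to pass.** The observed loss over 36 weeks must be below 36 x (0.055 - 1.96 x SE): 0.92, 0.57 or 0.22 points for the three SEs.

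**Direct check at week 80.** With SD 13 and 167 per group, the SE is 13 x √(2/167) = 1.42. A difference of about 1.96 x 1.42 = 2.8 points is needed for significance.

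**The case against.** **The margin does its job.** A pass excludes a 2-point loss; it does not permit one. A true loss at the margin gets through in about 2% of trials, and the observed loss must be well under 1 point at the assumed SEs. If half of a 0.10/week gain were being lost, both legs would pass in only 4 to 5% of trials. All of this stands, and it answers the stronger reading that the margin is too wide.

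**The margin looks reasoned.** It matches 50% retention of 4 points over 36 weeks. The article does not say so, but it is a condensed account that points to a full protocol, so a missing rationale is no fault here. This also stands. Such a rationale, however, would support a claim of retaining about half of a 4-point gain, not a claim of equality.

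**Tempting comparisons with the planning figures fail.** A reader might set the margin against 3/80 = 0.0375 or 4/80 = 0.05 points/week and conclude that it exceeds the anticipated rates. The 3 points ("31 points (worsening of 3 points during follow-up") are a net change from untreated baseline to week 80, so early symptomatic improvement is mixed in. The 4 points are a week 80 difference that the design expects to arise in phase 1. Neither is a phase 2 slope.

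**The rest of the plan covers it.** Week 80 is the primary outcome and tests directly what remains. The article calls a pass only indicative, and it promises 95% confidence intervals throughout. These points soften the consequence. They do not repair the rule, which does not make the disease-modification inference depend on week 80.

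**Conclusion.** The inference is wrong as worded. A pass supports the statement that early start does not progress faster than delayed start by 0.055 points/week or more, that is, a relative loss below 1.98 points over weeks 44 to 80 (49.5% of the 4-point target). It does not support equality. For a phase 1 gain of about 2 points or less, it does not by itself exclude complete loss of the gain.

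The 1.98 figure follows from the article's own numbers and assumes linear slopes. The direction of the test is inferred from context, since the article states only a margin on the slope difference. The 38%, 20% and 11% pass rates depend on assumed SEs and on a gain well below the planned one. They illustrate the problem and are not estimates for this trial.

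A reader might infer that the margin should be tightened, or that the trial is likely to declare a lasting effect that is fully vanishing. The documents support neither. The fault lies in the stated conclusion of a secondary analysis, and it can be corrected by wording.

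**What to change.** Keep the test and the margin, and change what is concluded:

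1. Replace the language of equality, in both the description of the phase 2 test and the inference rule, by: *early start loses less than 2.0 UPDRS points relative to delayed start over weeks 44 to 80*.
2. Report the phase 1 gain and the phase 2 loss side by side in points (36 x slope difference), each with a 95% confidence interval.
3. Call the effect maintained or disease modifying only when the pass is read together with the week 80 between-group difference, or when a confidence interval for phase 1 gain minus phase 2 loss excludes zero. That interval must carry the uncertainty of both estimates.

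On item 3, comparing the upper limit of the loss with the estimated gain would not be enough, because it treats a noisy gain as fixed. In the scenario with a gain of 0.06/week and half being lost, it lowers the pass rates only from 38%, 20% and 11% to about 31%, 18% and 11%.

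**Cost.** No patients or visits are added, and the power of the slope test is unchanged. The claim after a pass becomes less favourable, and the label is harder to earn for modest gains. With independent estimates and an SE of 0.015 in each phase, gain minus loss must exceed 1.96 x √2 x 0.015 x 36 = 1.5 points; at 0.020 it must exceed 2.0 points, and at 0.025, 2.5 points.
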